### Primary study factors

-Change in maternal BMI from pre-pregnancy to birth-Maternal BMI (either pre-pregnancy BMI or BMI at birth as outlined below)

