### Secondary outcomes

Secondary outcomes were clinically relevant outcomes available in the dataset.

Maternal
-Third- or fourth-degree perineal laceration-Instrumental vaginal delivery-Diabetes in pregnancy (pre-existing type 1 or type 2 diabetes or gestational diabetes)-Pre-term delivery-Hypertensive disorders in pregnancy-Induction of labour-Augmentation of labour-Chorioamnionitis in labour-Unplanned hysterectomy-Blood transfusion-Admission to intensive care unit (ICU)-Trial of labour

Neonatal
-Birth weight >90th percentile-Birth weight <10th percentile-Apgar Score < 6 at 5 min-Assisted Ventilation immediately following delivery-Assisted ventilation required for more than 6 h-Neonatal intensive care unit (NICU) admission-Antibiotics received for suspected neonatal sepsis-Seizure or serious neurological dysfunction-Infant breastfed at discharge

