### Variables

Mean and standard deviation (SD) will be used to describe continuous variables if they are normally distributed, otherwise median, and interquartile range (IQR) will be used. Categorical variables will be reported as numbers and percentages.

Gestational BMI gain in kgm^-2^ will be reported in the primary analysis. GWG in kg will be analysed for the sensitivity analysis.

Variables will be measured/described as follows:-Gestational BMI gain in kgm^-2^ (for the main analysis). Analysed as a linear spline with a knot at 5 kgm^-2^ based on preliminary analysis of 2022 data.-Self-reported pre-pregnancy BMI in kgm^-2^ (based on height and self-reported pre-pregnancy weight) classified according to the Institute of Medicine (IOM) groups [15]-Measured BMI at birth in kgm^-2^ classified into groups of the same size as pre-pregnancy BMI to account for expected weight gain during pregnancy-GWG in kg (for the sensitivity analysis)-Parity (categorized as nulliparous, or parous)-Maternal age in years (as a continuous variable, with linearity observed in the preliminary analysis of the 2022 data)-Gestational age at birth in weeks (categorized by gestational week)-Maternal height in cm (as a continuous variable, with linearity observed in the preliminary analysis of the 2022 data)-Maternal race (to be categorized as the dataset allows)-Maternal cigarette smoking during pregnancy (to be categorized as the dataset allows)-Payment type (public/private)-Trimester of onset of maternity care (first/second/third trimester/no antenatal care)-Maternal education (categorized as (i) 8th grade or less, (ii) 9th-12th grade, no diploma, (iii) completed high school or GED, some college credit or associate degree, (iv) bachelor’s degree, (v) masters degree, doctorate or professional degree)-Any fertility treatment used in conception (yes, no, unknown)-Diabetes in pregnancy (to be categorized as the dataset allows)-Hypertensive disorders in pregnancy (to be categorized as the dataset allows)-Previous preterm birth (yes, no)

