### Analysis plan

Data will be downloaded from the CDC website (https://www.cdc.gov/nchs/data_access/vitalstatsonline.htm) for the most recent year with available data (2023 at the time of writing this protocol).

If data missingness for one or more explanatory or outcome variables occurs in > 5 % and < 40 % eligible births then multiple imputation will be considered. Potential mechanisms of missingness and the relationship of missingness to the outcome and covariates will be assessed when deciding to conduct multiple imputation or a complete case analysis.

If multiple imputation is required, we will use fully conditional specification with five imputed datasets. Any multiple imputation will include all explanatory and outcome variables, and any interaction terms. Interdependencies amongst variables will be handled with the passive imputation method. P-values for the likelihood ratio test for each variable in each imputed dataset will be pooled using the median p-value rule.

Using Robust Poisson Regression, maternal pre-pregnancy BMI will be modelled on the primary outcome of cesarean delivery and other covariates (listed below) excluding BMI gain during pregnancy. Maternal BMI at the time of delivery will be modelled on the same covariates. Of these two models, the model with the lowest Akaike Information Criterion (AIC) will be used to select the BMI variable with the greatest explanatory power to be used in subsequent analyses (either pre-pregnancy or delivery BMI). This variable is referred to as ‘Maternal BMI’ in all subsequent analyses below. The two models will also be compared using the log-likelihood test.

Pre-pregnancy BMI will be categorized according to the United States Centers for Disease Control and Prevention which classifies adult BMI as underweight (BMI < 18.5), normal weight (BMI 18.5 – 24.9), overweight (BMI 25-19.9), Class 1 obesity (BMI 30-34.9), Class 2 Obesity (BMI 35-39.9), and Class 3 Obesity (BMI 40 or more) [20]. Delivery BMI will be classified such that the same numbers of women will be in each class (i.e., the same quantile cut-offs will be used for pre-pregnancy and delivery BMI groups). This is expected to account for weight gain in pregnancy including factors such as fetal weight and amniotic fluid volume. Based on the exploratory analysis for 2022 data, BMI gain and gestational weight gain will be treated as linear splines with one knot placed at 5 kgm^-2^ and at 12 kg respectively.

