As nulliparous women are an important group who contribute to the first/primary cesarean delivery rate, we will test for interaction (effect modification) between maternal BMI gain and parity, and maternal BMI and parity. If interaction is present (BMI or BMI gain have a different association with cesarean delivery depending on parity), then the primary analysis will be restricted to nulliparous women only and we will conduct secondary analyses for parous women.

For the primary outcome of cesarean delivery, backward stepwise Robust Poisson Regression will be used. The following variables will be included in the multivariable Poisson regression model as potential predictors of cesarean section:•Maternal BMI (not eligible for exclusion in the backwards stepwise regression).•Gestational BMI gain (not eligible for exclusion in the backwards stepwise regression)•Parity•Maternal age (continuous)•Gestational age•Maternal height•Maternal race•Cigarette smoking•Payment type•Trimester of onset of maternity care (4 categories: first, second or third trimester, or no•antenatal care)•Education (categorized)•Fertility treatment used•Diabetes (3 categories: pre-pregnancy, gestational, none)•Hypertension in pregnancy (dichotomous)•Interaction terms: BMI x parity and BMI gain x parity

Birthweight will not be included as an explanatory variable because it was considered that fetal weight may be on the causal pathway between BMI or BMI gain and cesarean delivery. Therefore, the relative risks for BMI or BMI gain for the primary outcome of cesarean delivery will include any indirect effect mediated through fetal weight.

If Robust Poisson Regression Models do not converge then alternative regression methods will be considered.

For secondary outcomes, all explanatory variables will be retained in the model. Stepwise backward regression will not be used. No interaction terms will be used.

For the secondary outcome of third or fourth degree perineal laceration, the data will be limited to vaginal births only and the following covariates will be used: BMI at delivery, BMI gain, parity, maternal age, gestational age, maternal height, maternal race, mode of delivery (unassisted/vacuum/forceps).

For the secondary outcome of trial of labour, the following covariates will be used: BMI at delivery, BMI gain, parity, maternal age, gestational age, maternal height, maternal race, payment type, education, trimester of onset of maternity care, use of ARTs, and gestational diabetes.

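### BMI gain includes the baby's own weight, so the two birthweight-percentile outcomes carry a built-in association with it

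*Protocol article*

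**What the plan says.** Under Primary study factors the exposure is "Change in maternal BMI from pre-pregnancy to birth". The Variables section takes the end point of that change from BMI measured at birth and enters gain as a continuous term: "Analysed as a linear spline with a knot at 5 kgm^-2^ based on preliminary analysis of 2022 data". Nothing is subtracted for the baby.

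Secondary outcomes (neonatal) lists "Birth weight >90th percentile" and "Birth weight <10th percentile". The Analysis plan gives no model specific to these two. The general rule therefore applies: "For secondary outcomes, all explanatory variables will be retained in the model". BMI gain stays in both models.

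The plan does recognise that delivery weight contains the fetus, but only when it explains the delivery-BMI categories, which use the same quantile cut-offs as pre-pregnancy BMI: "This is expected to account for weight gain in pregnancy including factors such as fetal weight and amniotic fluid volume". For cesarean, birthweight is left out of the model as a possible intermediate, and the plan says: "Therefore, the relative risks for BMI or BMI gain for the primary outcome of cesarean delivery will include any indirect effect mediated through fetal weight". The sensitivity analysis replaces BMI gain with gestational weight gain in kg. The Limitations section does not mention any overlap between gain and birthweight.

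**The concern.** Gain is delivery weight minus pre-pregnancy weight, over height squared. Delivery weight is the mother's own weight plus fetus, placenta and fluid. Take two mothers with identical tissue gain, one carrying a baby 1 kg heavier: her recorded gain is 1 kg higher. When the outcome is whether the baby is heavy or light for the population, part of the outcome sits inside the predictor.

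The direction is fixed: total gain will look positively related to large babies and negatively related to small ones, whatever the biology. With several hundred thousand births it will also be highly significant. The study sets out to ask whether gain, as opposed to BMI, matters for outcomes (Uniqueness of the study). For these two outcomes a reader could not separate an effect of maternal gain from arithmetic.

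None of the planned steps removes this:
- Quantile cut-offs move category boundaries for the whole population and leave each individual's gain unchanged.
- Gestational weight gain in kg contains the fetus too.
- Adjusting for gestational week leaves the variation in birthweight within a week.

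**Working it through.** **Inputs from the protocol (Sample size).** Cesarean rate 18.17% overall and 27.40% in nulliparous women; target one percentage point per kg/m² of gain; largest required sample 716,392. The target relative risks are 19.17/18.17 = 1.055 and 28.40/27.40 = 1.0365. The required sample itself cannot be reproduced, because the R² values, category prevalences and SD of gain are not printed. The point does not depend on it.

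**Assumed inputs, not in the documents.** Height 1.63 m (h² = 2.657); birthweight SD at fixed gestation s_b = 0.40–0.50 kg; SD of gain without the baby s_o = 5–8 kg; both normal and independent of each other. Independence means the true association between maternal gain and birthweight is nil.

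**Formula.** For a normal exposure G, the log-linear Poisson slope is b = (mean of G among cases − overall mean of G) / variance of G. For birthweight above its 90th percentile, the cases' mean birthweight lies 1.755 SD above average (normal density at 1.2816, which is 0.1755, divided by 0.10). Since G contains birthweight/h²,

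b = 1.755 × s_b × h² / (s_b² + s_o²),

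and for the 10th percentile the slope is −b.

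| s_b | s_o | correlation of birthweight with gain | b | RR >90th | RR <10th |
|---|---|---|---|---|---|
| 0.40 | 8 | 0.050 | 1.755×0.40×2.657/64.16 = 0.029 | 1.03 | 0.97 |
| 0.45 | 6.5 | 0.069 | 1.755×0.45×2.657/42.45 = 0.049 | 1.05 | 0.95 |
| 0.50 | 5 | 0.100 | 1.755×0.50×2.657/25.25 = 0.092 | 1.10 | 0.91 |

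**Simulation check.** Robust Poisson regression on 716,392 simulated births with one linear gain term gave 1.028 to 1.096 for >90th and 0.912 to 0.970 for <10th. In the central setting z was about 34 and −35. With birthweight subtracted from gain, all relative risks returned to 0.998–1.002.

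With the planned spline (knot at 5 kg/m²) in the central setting, the false relative risks below and above the knot were 1.057 and 1.047 for >90th, and 0.952 and 0.952 for <10th. Net gain gave 0.999–1.002. The spline does not absorb the artefact.

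**Cesarean.** Suppose birthweight raises cesarean risk by a factor q per SD, independently of maternal gain (q = 1.1–1.4, assumed). Then b = ln(q) × s_b × h² / (s_b² + s_o²).
- Smallest: 0.0953×0.40×2.657/64.16 = 0.0016, RR 1.002.
- Central (q = 1.2): 0.1823×0.45×2.657/42.45 = 0.0051, RR 1.005.
- Largest: 0.3365×0.50×2.657/25.25 = 0.0177, RR 1.018.

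The simulated values ran from 1.000 to 1.018. Most are well below the targets of 1.0365 and 1.055.

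**The case against.** **The overlap is a tiny share of gain.** True in variance terms: a correlation of 0.05–0.10 means the baby accounts for 1% or less of the variance of total gain, and the large z-values reflect the sample size. But the reported quantity is the relative risk per kg/m². A false value near 1.05 is not trivial beside a study sized on 1.0365–1.055.

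**Total gain is the intended exposure, and the aim is partly descriptive.** This stands as a reason to keep total gain in the report. It does not help a reader who takes the birthweight results as evidence about maternal gain and fetal growth.

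**Net gain has its own faults.** Placenta and fluid remain in it. Subtracting birthweight also assumes that the recorded delivery weight contains the full fetal weight; where it does not, subtraction creates some coupling in the opposite direction. The return to 1.00 in simulation follows from the independence built into it. This is why net gain should sit beside total gain and not replace it.

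**Scope.** These are two among many secondary outcomes, with no power claim attached.

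**A stronger reading that the documents do not support.** A reader might infer that the plan wrongly treats fetal weight as nothing but a mediator for cesarean, so that the primary analysis is flawed. The Analysis plan says only that fetal weight may lie on the pathway and that the relative risks include any such effect. For gain that is incomplete, but it is not false: gain may also act through fetal growth, and a total association does include any mediated part. Restricting the sentence to BMI would be wrong as well, because the selected BMI term may be delivery BMI, which contains the fetus too.

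**Conclusion.** The point holds for the two birthweight-percentile outcomes. The overlap follows from the protocol's own definitions and nothing planned removes it. Its direction needs no assumption beyond the fetus being part of delivery weight. Its size, about 1.03–1.10 per kg/m² for >90th and 0.91–0.97 for <10th percentile, rests on the assumed SDs and height, and on models without the other covariates.

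For cesarean the same arithmetic gives about 1.00–1.02 per kg/m² under a further assumed effect of birthweight. That shows no material defect in the primary analysis, and leaving birthweight out of that model is defensible. Pre-pregnancy BMI is unaffected; delivery BMI shares the overlap.

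**What to change.** For birth weight >90th and <10th percentile:
- Also fit gain net of the baby, (delivery weight − pre-pregnancy weight − birthweight)/height². Report it beside total gain, and base any statement about maternal gain and fetal size on the net-gain result.
- If delivery BMI would be the BMI term in these two models, use pre-pregnancy BMI there.

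For cesarean, at most add a sentence to the Analysis plan: fetal weight is also an arithmetic component of BMI gain and of delivery BMI, so the relative risks include that overlap as well as any mediated effect. Leave the existing mediation statement applying to both BMI and gain.

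The cost is one derived variable (birthweight is already needed to define the outcomes), one additional model for each of the two outcomes, and a second exposure definition to explain. Placenta and fluid stay in net gain, and it is sensitive to error in the recorded delivery weight; both should be stated.

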### Data collection and methods

Publicly available data from the United States Centers for Disease Control and Prevention (CDC) will be used and will be downloaded from https://www.cdc.gov/nchs/data_access/vitalstatsonline.htm[18].

Variables that are a planned part of the analysis will be interrogated to describe any missingness and extreme outliers.

### Variables

Mean and standard deviation (SD) will be used to describe continuous variables if they are normally distributed, otherwise median, and interquartile range (IQR) will be used. Categorical variables will be reported as numbers and percentages.

Gestational BMI gain in kgm^-2^ will be reported in the primary analysis. GWG in kg will be analysed for the sensitivity analysis.

Variables will be measured/described as follows:-Gestational BMI gain in kgm^-2^ (for the main analysis). Analysed as a linear spline with a knot at 5 kgm^-2^ based on preliminary analysis of 2022 data.-Self-reported pre-pregnancy BMI in kgm^-2^ (based on height and self-reported pre-pregnancy weight) classified according to the Institute of Medicine (IOM) groups [15]-Measured BMI at birth in kgm^-2^ classified into groups of the same size as pre-pregnancy BMI to account for expected weight gain during pregnancy-GWG in kg (for the sensitivity analysis)-Parity (categorized as nulliparous, or parous)-Maternal age in years (as a continuous variable, with linearity observed in the preliminary analysis of the 2022 data)-Gestational age at birth in weeks (categorized by gestational week)-Maternal height in cm (as a continuous variable, with linearity observed in the preliminary analysis of the 2022 data)-Maternal race (to be categorized as the dataset allows)-Maternal cigarette smoking during pregnancy (to be categorized as the dataset allows)-Payment type (public/private)-Trimester of onset of maternity care (first/second/third trimester/no antenatal care)-Maternal education (categorized as (i) 8th grade or less, (ii) 9th-12th grade, no diploma, (iii) completed high school or GED, some college credit or associate degree, (iv) bachelor’s degree, (v) masters degree, doctorate or professional degree)-Any fertility treatment used in conception (yes, no, unknown)-Diabetes in pregnancy (to be categorized as the dataset allows)-Hypertensive disorders in pregnancy (to be categorized as the dataset allows)-Previous preterm birth (yes, no)

### Sample size

To estimate R^2^, pre-pregnancy BMI group and BMI gain were regressed on the other explanatory variables using equivalent US birth data for the preceding year (2022). As pre-pregnancy BMI was categorized according to IOM groups, dummy variables were created with normal BMI (18.5 to < 25) as the referent category, and each of these was regressed on the remaining dummy variables, the two BMI gain spline variables, and the other explanatory variables, resulting in five R^2^ estimations. As BMI gain was a linear spline with one knot, the two BMI gain spline terms were regressed on the five BMI group dummy variables, the remaining BMI gain spline variable, and the other explanatory variables, resulting in an additional two R^2^ estimations. These R^2^ estimations were repeated for nulliparous women only, resulting in 14 R^2^ estimations in total.

We specified an alpha value of 0.05 and beta value of 0.10, and a cesarean section rate of 18.17 % at the mean gestational BMI gain based on US birth data for 2022. This cesarean section rate was 27.40 % for nulliparous women only. We aimed to detect an increase in the cesarean section rate of one percentage point for each BMI category compared with the referent category (18.5 to < 25) (e.g., relative risk 19.17 %/18.17 %), and an increase in the cesarean section rate of one percentage point per kgm^-2^ of BMI gain. R^2^ values were used to calculate the variance inflation factor using the method described Signorini (1991) for calculating the sample size based on an exact Poisson Regression [19]. These calculations were performed using the pwrss package (Version 0.3.1) in R (Version 4.4.0).

The largest sample sizes required were:•For the full sample including nulliparous and parous women: required sample size = 570,014•For nulliparous women only: required sample size = 716,392

Based on the numbers of births in the 2022 data, we expect there will be enough births in the 2023 data to meet these required sample sizes

### Analysis plan

Data will be downloaded from the CDC website (https://www.cdc.gov/nchs/data_access/vitalstatsonline.htm) for the most recent year with available data (2023 at the time of writing this protocol).

If data missingness for one or more explanatory or outcome variables occurs in > 5 % and < 40 % eligible births then multiple imputation will be considered. Potential mechanisms of missingness and the relationship of missingness to the outcome and covariates will be assessed when deciding to conduct multiple imputation or a complete case analysis.

If multiple imputation is required, we will use fully conditional specification with five imputed datasets. Any multiple imputation will include all explanatory and outcome variables, and any interaction terms. Interdependencies amongst variables will be handled with the passive imputation method. P-values for the likelihood ratio test for each variable in each imputed dataset will be pooled using the median p-value rule.

Using Robust Poisson Regression, maternal pre-pregnancy BMI will be modelled on the primary outcome of cesarean delivery and other covariates (listed below) excluding BMI gain during pregnancy. Maternal BMI at the time of delivery will be modelled on the same covariates. Of these two models, the model with the lowest Akaike Information Criterion (AIC) will be used to select the BMI variable with the greatest explanatory power to be used in subsequent analyses (either pre-pregnancy or delivery BMI). This variable is referred to as ‘Maternal BMI’ in all subsequent analyses below. The two models will also be compared using the log-likelihood test.

Pre-pregnancy BMI will be categorized according to the United States Centers for Disease Control and Prevention which classifies adult BMI as underweight (BMI < 18.5), normal weight (BMI 18.5 – 24.9), overweight (BMI 25-19.9), Class 1 obesity (BMI 30-34.9), Class 2 Obesity (BMI 35-39.9), and Class 3 Obesity (BMI 40 or more) [20]. Delivery BMI will be classified such that the same numbers of women will be in each class (i.e., the same quantile cut-offs will be used for pre-pregnancy and delivery BMI groups). This is expected to account for weight gain in pregnancy including factors such as fetal weight and amniotic fluid volume. Based on the exploratory analysis for 2022 data, BMI gain and gestational weight gain will be treated as linear splines with one knot placed at 5 kgm^-2^ and at 12 kg respectively.

As nulliparous women are an important group who contribute to the first/primary cesarean delivery rate, we will test for interaction (effect modification) between maternal BMI gain and parity, and maternal BMI and parity. If interaction is present (BMI or BMI gain have a different association with cesarean delivery depending on parity), then the primary analysis will be restricted to nulliparous women only and we will conduct secondary analyses for parous women.

For the primary outcome of cesarean delivery, backward stepwise Robust Poisson Regression will be used. The following variables will be included in the multivariable Poisson regression model as potential predictors of cesarean section:•Maternal BMI (not eligible for exclusion in the backwards stepwise regression).•Gestational BMI gain (not eligible for exclusion in the backwards stepwise regression)•Parity•Maternal age (continuous)•Gestational age•Maternal height•Maternal race•Cigarette smoking•Payment type•Trimester of onset of maternity care (4 categories: first, second or third trimester, or no•antenatal care)•Education (categorized)•Fertility treatment used•Diabetes (3 categories: pre-pregnancy, gestational, none)•Hypertension in pregnancy (dichotomous)•Interaction terms: BMI x parity and BMI gain x parity

Birthweight will not be included as an explanatory variable because it was considered that fetal weight may be on the causal pathway between BMI or BMI gain and cesarean delivery. Therefore, the relative risks for BMI or BMI gain for the primary outcome of cesarean delivery will include any indirect effect mediated through fetal weight.

If Robust Poisson Regression Models do not converge then alternative regression methods will be considered.

For secondary outcomes, all explanatory variables will be retained in the model. Stepwise backward regression will not be used. No interaction terms will be used.

For the secondary outcome of third or fourth degree perineal laceration, the data will be limited to vaginal births only and the following covariates will be used: BMI at delivery, BMI gain, parity, maternal age, gestational age, maternal height, maternal race, mode of delivery (unassisted/vacuum/forceps).

For the secondary outcome of trial of labour, the following covariates will be used: BMI at delivery, BMI gain, parity, maternal age, gestational age, maternal height, maternal race, payment type, education, trimester of onset of maternity care, use of ARTs, and gestational diabetes.

For the secondary outcome of preterm birth, the same covariates will be used as for the primary outcome except gestational age will be removed and previous preterm birth will be added.

For the secondary outcome of NICU admission, the same covariates will be used as for the primary outcome of cesarean delivery.

For the uncommon or rare secondary outcomes of unplanned hysterectomy, maternal admission to the ICU, 5 min Apgar Score < 4, assisted ventilation immediately following delivery and for more than six hours, antibiotics for suspected neonatal sepsis, and neonatal seizure or serious neurological dysfunction, the same covariates will be used as for the primary outcome, if there are at least five events per variable. If there are fewer than five events per variable, then we will preselect a smaller group of the most relevant covariates or conduct a univariable analysis.

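### If multiple imputation is used and much information is missing, a fixed five imputations leaves standard errors and borderline p-values dependent on the random seed; tying the number to the missingness is a cheap improvement

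*Protocol article*

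**What the plan says.** All the relevant text is in the Analysis plan of the protocol article.

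- **Trigger.** The rule begins "If data missingness for one or more explanatory or outcome variables" and continues "occurs in > 5 % and < 40 % eligible births then multiple imputation will be considered". The limits apply to each variable separately, and imputation is an option, not a commitment.
- **Alternative.** Mechanisms of missingness and their relation to outcome and covariates "will be assessed when deciding to conduct multiple imputation or a complete case analysis".
- **Number.** If imputation goes ahead, it is "fully conditional specification with five imputed datasets". No reason, precision target or link to the amount of missing data is given.
- **P-values.** Likelihood ratio p-values for each variable "will be pooled using the median p-value rule". With five datasets, the pooled value is the third-ranked of five.
- **Where p-values are used.** For the primary outcome, "backward stepwise Robust Poisson Regression will be used". Maternal BMI and BMI gain are protected from removal. The two parity interaction terms are in the model, and if interaction is judged present the primary analysis is confined to nulliparous women. Secondary outcomes use no stepwise selection.

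Under Sensitivity analysis, the final model from the imputed data is to be refitted in the complete data.

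**The concern.** Five imputations estimate the between-imputation variance from five values. When little information is missing, that variance is a small part of the total and a poor estimate of it does no harm. When much is missing, it is a large part, and the reported standard error then depends noticeably on the random number seed.

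Two analysts following the same plan with different seeds could then report visibly different confidence intervals. They could also decide a borderline covariate or a borderline parity interaction differently. The interaction decision matters most, because it determines whether the primary analysis covers all women or only nulliparous women. Uncommon secondary outcomes are also exposed, because their intervals are wider and effects are more likely to lie near a threshold.

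**Working it through.** **Inputs.** m = 5 and the per-variable range of above 5% to below 40% come from the Analysis plan. Alpha 0.05 and power 0.90 come from Sample size. Four things are assumed:
- FMI is 0.05, 0.10, 0.20 or 0.40. The documents give no FMI; these values use the missingness limits as a rough guide, and the true FMI may be lower or higher.
- Estimates and standard errors are pooled by Rubin's rules, which the article does not state.
- The significance threshold is two-sided 0.05.
- The parity interaction terms are pooled by the same median rule as the other terms.

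The plan gives no calculation behind five, so there is no figure to reproduce.

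**Seed-to-seed CV of the standard error** ≈ FMI / √(2(m − 1)).

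| FMI | m = 5 (divide by √8 = 2.828) | m = 40 (divide by √78 = 8.832) |
|---|---|---|
| 0.05 | 1.8% | 0.6% |
| 0.10 | 3.5% | 1.1% |
| 0.20 | 7.1% | 2.3% |
| 0.40 | 14.1% | 4.5% |

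**Other quantities at FMI 0.40**
- Relative efficiency = 1/(1 + FMI/m): 1/1.08 = 0.926 with m = 5; 1/1.01 = 0.990 with m = 40.
- Monte Carlo error of the estimate = √(FMI/m), in standard errors: √0.08 = 0.28 with m = 5; √0.01 = 0.10 with m = 40.
- Rubin degrees of freedom = (m − 1)/λ², where λ = (1 + 1/m)B/T. Take between-imputation variance B = 0.4 and within-imputation variance 0.6. With m = 5, T = 0.6 + 1.2 × 0.4 = 1.08, λ = 0.48/1.08 = 0.444, and 4/0.1975 ≈ 20. With m = 40, T = 0.6 + 1.025 × 0.4 = 1.01, λ = 0.41/1.01 = 0.406, and 39/0.1648 ≈ 237.

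**Number needed for a 5% CV**: m = 1 + 0.5 × (FMI/0.05)². This gives 33 at 0.40 (1 + 0.5 × 64), 19 at 0.30, 9 at 0.20, 3 at 0.10 and 2 at 0.05.

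**Simulation** (40,000 re-imputations of fixed data, FMI 0.40; ranges are 5th to 95th percentile over seeds; z is the value with unlimited imputations).

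| Quantity | m = 5 | m = 40 |
|---|---|---|
| SE relative to its limiting value | 0.83 to 1.32 | 0.93 to 1.08 |
| z = 1.96: Rubin p | 0.011 to 0.21 | 0.030 to 0.084 |
| z = 1.96: median p | 0.001 to 0.071 | 0.005 to 0.023 |
| z = 2.5: Rubin p | 0.002 to 0.106 | 0.006 to 0.026 |
| z = 2.5: seeds with Rubin p < 0.05 | 77.5% | essentially 100% |
| z = 2.5: seeds with median p < 0.05 | 99.8% | 100% |

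At z = 5 or more, every seed gives p < 0.05 under both pooling methods, with m = 5 as well as m = 40.

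**The study's own design effect.** For nulliparous women, the Sample size section targets 28.40% against 27.40%. At 90% power the complete-data z is 1.96 + 1.28 = 3.24. At FMI 0.40 it falls to 3.24 × √0.6 = 2.51. With m = 5, the seed-to-seed SD of the lower confidence limit of the relative risk is about 0.001, 0.002, 0.0035 and 0.007 at FMI 0.05, 0.10, 0.20 and 0.40. The Rubin p-value is below 0.05 for over 99% of seeds at the first three, and for 78% at 0.40.

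**The case against.** The strongest reply is that this provision may never be used. Imputation is only to be considered, complete-case analysis is an explicit alternative, and actual missingness is not reported. If missingness is just above 5%, five imputations are enough. This stands, and it is why the point is conditional. A reader might infer that five is too few in any event, or that the study's results will not be reproducible; the documents support neither.

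A reader might also equate the 40% limit with an FMI of 0.40. The limit applies to single variables, including covariates such as smoking or education, and missing values in a covariate do not carry over one-for-one into the BMI coefficients. So 0.40 is an assumed upper case. Nor does a limit of 40% per variable imply that 40 imputations would match the share of incomplete births: with several incomplete variables, that share can exceed 40%.

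The effect on variable selection is narrower than it may look. BMI and BMI gain cannot be eliminated, and secondary outcomes involve no selection. What remains is the adjustment covariates and the parity interactions, and only near the threshold. With the sample sizes planned, strong effects are safe.

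The complete-data refit means the imputed results will not stand alone, but it does not measure Monte Carlo error and so does not answer the point.

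**Conclusion.** The point holds as a minor, conditional improvement. The plan fixes one number of imputations for a range in which the adequate number, on the assumed FMI values, runs from about 2 to about 33 for a 5% CV of the standard error. With five, seed dependence is negligible at an FMI of 0.05 to 0.10, noticeable at 0.20 (CV about 7%) and material at 0.40 (about 14%). Loss of efficiency is not the main issue, since it is still 0.926 at 0.40. What suffers is the stability of intervals and of borderline decisions, above all the parity interaction test.

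This rests on the assumed FMI, on Rubin pooling and on a 0.05 threshold.

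A reader might infer that more imputations would also put the median p-value rule right. They would not. At FMI 0.40 and z = 1.96, where the limiting p-value is 0.05, the median p-value with m = 40 still lies between 0.005 and 0.023, because each p-value entering the median ignores between-imputation variance. That is a separate matter.

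**What to change.** In the Analysis plan, replace the fixed five with a rule: at least 20 imputed datasets, raised according to the observed share of births with any missing analysis variable or the estimated FMI. About 33 would hold the CV of the standard error to 5% at FMI 0.40. State a fixed seed, and report the Monte Carlo error of the main estimates and of the parity interaction p-values. The 2023 file is public, so missingness can be tabulated before any outcome model is fitted.

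The cost is computing time: every step of the backward elimination and each secondary outcome model must be refitted in more copies of a file of several hundred thousand births. If the median p-value rule is kept, it should be taken over the larger number of datasets, with a note that this steadies the pooled p-value but does not bring in the between-imputation variance.
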